#### Sub-study 2: community cohort

PICO framework (table 1).

### Index date

The index date will be defined as the date of admission to a psychiatric hospital.

### Outcomes

Outcome measures are the length of hospital stay (number of days), and clinical and functional improvement while in hospital. The Health of the Nation Outcome Scales (HoNOS) is a clinician-rated clinical and social functioning assessment scale with 12 items, each rated between 0 (no problem) and 4 (very severe problem).^16^ It has good psychometric properties.^17 18^ The HoNOS is routinely recorded by NHS staff at intervals and at points of care transition (eg, hospital admission and discharge).

### Inclusion and exclusion criteria

All eligible patients who were admitted to a psychiatric hospital for at least 14 days may be included in this study. We will exclude people who were not open to a SLaM community team for at least 6 months prior to their admission, as these people may have a high degree of missing data and may not have had an opportunity for a community C(E)TR before their admission or might represent new transfers from other NHS Trusts. We will also exclude ‘re-admissions’, defined as an admission occurring <6 months after the discharge date of a previous admission.

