#### Sub-study 1: community cohort

Population, Intervention, Comparison and Outcome (PICO) framework (table 1).

**Table 1 T1:** Population, Intervention, Comparison and Outcome framework for sub-studies 1 and 2

	Sub-study 1	Sub-study 2
Population	People of any age with a recorded diagnosis of intellectual disability (ICD-10 code F7x), autism (ICD-10 code F84) or both, with at least 1 year of care under secondary mental healthcare services	People of any age with a recorded diagnosis of intellectual disability (ICD-10 code F7x), autism (ICD-10 code F84) or both, with at least 1 year of care under secondary mental healthcare services and an admission to a psychiatric inpatient ward for a period of at least 14 days
Intervention	Community C(E)TR	Community C(E)TR within 6 months prior to admission
Comparison	No community C(E)TR	Did not receive a community C(E)TR within 6 months prior to admission
Outcome		
Primary	Psychiatric hospital inpatient admission within 6 months of the community C(E)TR	Length of psychiatric hospital admission (days)
Secondary	Descriptive data and comparison of baseline demographics between intervention and comparison groups	Descriptive data and comparison of baseline demographics between intervention and comparison groups
	Descriptive data of 6 months pre-C(E)TR/post-C(E)TR (index date): neuropsychiatric symptoms, clinical variables and service use	Descriptive data and comparison of prehospital admission neuropsychiatric symptoms, HoNOS and service use Clinical and social functional improvement (change in HoNOS) while in hospital

C(E)TR, Care (Education) and Treatment Review; HoNOS, Health of the Nation Outcome Scales.

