#### Time-to-event analysis

Time-to-discharge (length of hospital admission) will be analysed using the Kaplan-Meier estimator.^19^ A Cox’s proportional hazards model will be used to estimate the HR for discharge,^20^ comparing those who received a C(E)TR to those who did not receive a C(E)TR for a follow-up period of 6 months after admission. This analysis will be adjusted for C(E)TR status prior to admission, age at admission, sex, ethnicity and relevant diagnosis at admission (intellectual disability with/without autism, or autism alone). Patients who die within 6 months of admission will be censored at the date of death, and patients who remain in hospital will be censored at the end of the 6 months.

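### Sub-study 2 keeps only stays of at least 14 days although length of stay is its primary outcome, so its comparison holds only for people still in hospital at day 14

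*Protocol article*

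**What the plan says.** The entry rule appears twice. Sub-study 2, Inclusion and exclusion criteria: "All eligible patients who were admitted to a psychiatric hospital for at least 14 days may be included in this study". Table 1, Population row for sub-study 2: "an admission to a psychiatric inpatient ward for a period of at least 14 days".

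Table 1 names length of psychiatric admission, in days, as the primary outcome of sub-study 2. The clock starts at admission: "The index date will be defined as the date of admission to a psychiatric hospital". Under Time-to-event analysis: "Time-to-discharge (length of hospital admission) will be analysed using the Kaplan-Meier estimator", and "A Cox’s proportional hazards model will be used to estimate the HR for discharge", "comparing those who received a C(E)TR to those who did not receive a C(E)TR for a follow-up period of 6 months after admission". On censoring, "patients who remain in hospital will be censored at the end of the 6 months".

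Exposure is a community C(E)TR in the 6 months before admission (Table 1). According to the Introduction, where admission is needed the panel sets out its purpose and prompts early planning for discharge, so that the stay is as short as possible.

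**The concern.** Whether a stay reaches 14 days is known only two weeks after time zero, and it is a value of the primary outcome. The exposure comes earlier and is intended to act on that same outcome, so it can change who passes the filter. If the C(E)TR works as intended, more admissions in the C(E)TR group than in the comparison group end before day 14 and are dropped. Those left in the two groups may then differ in ways that the planned adjustment (age, sex, ethnicity, diagnosis) does not capture.

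At stake is whether the result can be read as an answer to the aim in the Abstract, the effect of community C(E)TRs on length of hospital stay, or only as a comparison among people already in hospital for two weeks. The article does not state the second, narrower reading.

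**Working it through.** The article gives no length-of-stay distribution, effect size, event count or power for sub-study 2, so there is no figure to reproduce. From the article come the 14-day minimum, the origin at admission, the 6-month follow-up (182 or 183 days below) and the HR for discharge (above 1 means earlier discharge). Every distribution and effect below is an assumption.

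**Step 1. What the HR covers.** No one in the selected cohort can be discharged before day 14, so every risk set that contributes to the Cox likelihood lies from day 14 to 6 months. The HR is that of people still in hospital at day 14.

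**Step 2. Who is removed.** Take exponential stays with control median M and a constant HR of 1.5. The share removed is 1 − 2^(−14/M) in controls and 1 − 2^(−21/M) in the C(E)TR group (21 = 1.5 × 14).

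| M (days) | Controls removed | C(E)TR removed |
|---|---|---|
| 20 | 38% | 52% |
| 30 | 28% | 38% |
| 45 | 19% | 28% |
| 60 | 15% | 22% |

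Deletion differs by group whenever the exposure acts on early discharge.

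**Step 3. Medians from admission.** For exponential stays the median after the cut is 14 plus the uncut median. Medians of 30 and 20 days become 44 and 34, so a reduction of 10/30 = 33% reads as 10/44 = 23%, although the HR is unbiased.

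For lognormal stays with median M and log-SD 1.1, the share kept is S = Φ(ln(M/14)/1.1) and the median after the cut is M × exp(1.1 × Φ⁻¹(1 − S/2)). With every stay 30% shorter:
- Medians of 25 and 17.5 days become about 38.1 and 32.1, a reduction of 16%.
- Medians of 40 and 28 days become about 50.7 and 40.6, a reduction of 20%.

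**Step 4. The HR.** Large simulated groups, Cox model with one covariate, fitted to all admissions and again to stays of 14 days or more:

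| Assumed effect of the C(E)TR | HR, all admissions | HR, 14 days or more |
|---|---|---|
| Constant HR 1.5, exponential stays, control median 20-60 days | 1.50 | 1.48-1.50 |
| Every stay 30% shorter, lognormal, median 25-40, log-SD 1.1 | 1.34-1.37 | 1.24-1.31 |
| Conditional HR 2, gamma frailty variance 0.5, 1, 2, control median 30 | 1.63, 1.48, 1.33 | 1.50, 1.28, 1.14 |
| HR 2 in days 0-14, then 1, control median 20-60 | 1.18-1.41 | 1.00 |
| 30% of 14-60-day stays become 7-day stays, same lognormals | 1.07-1.14 | 0.86-0.89 |
| Two patient types, discharge faster in the short-stay type only (9 settings) | 1.05-1.35 | 0.65-0.93 |
| 30% of stays of 60 days or more halved, lognormal median 25; 40 | 1.07; 1.12 | 1.10; 1.13 |

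In the two-type case the short-stay share is 30, 50 or 70%. Its daily discharge hazard without and with a review is 0.05 and 0.15, 0.10 and 0.20, or 0.10 and 0.30. The other type has 0.01 in both groups. With a 50% share and 0.05 versus 0.15, the 182-day restricted mean difference moves from −7.0 to +13.5 days, although no patient's discharge was slowed.

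**Step 5. Events.** Assume 300 admissions, one sixth exposed, constant HR 1.5, exponential stays. With λ = ln 2/M, expected discharges by day 182 are:
- all admissions: 300 × [5/6 (1 − e^(−182λ)) + 1/6 (1 − e^(−273λ))]
- 14 days or more: 300 × [5/6 (e^(−14λ) − e^(−182λ)) + 1/6 (e^(−21λ) − e^(−273λ))]

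With D discharges, power is Φ(√(D × 5/36) × ln 1.5 − 1.96). At M = 30, D falls from 296 to 208: Φ(2.60 − 1.96) = 74% becomes Φ(2.18 − 1.96) = 59%. Across M = 20 to 60, discharges fall from 267-300 to 178-222 and power from 70-74% to 52-61%.

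**The case against.** The strongest defence is that the restriction is open and defines the population. Table 1 puts it in the Population row, the aims of sub-study 2 speak of comparing groups, and explicit causal modelling is kept for sub-study 1. Counting from admission rather than day 14 does not alter the HR, because the risk sets are the same. The analysis is in effect a day-14 landmark comparison, which is a coherent quantity. Under proportional hazards, the model the plan uses, the HR is not biased. All of this stands. It does not settle the matter: the Abstract speaks of effects on length of stay, no day-14 estimand is stated, the medians are distorted even under proportional hazards, and early discharges are lost.

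A reader might infer that the selection necessarily works against the C(E)TR group, or that the result will change sign. The documents do not support that. The Introduction says the review should help to shorten stays but does not place the benefit below 14 days, and shortening long stays fits the text equally well. In that case the cut slightly strengthens the HR. Reversal needs benefit concentrated in short stays, and the scenarios that show it were built that way.

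That the article gives no reason for 14 days is not itself a fault. The sensitivity analyses it describes belong to the causal framework of sub-study 1, and nothing in the article exempts the 12-month rerun from the 14-day rule.

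**Conclusion.** The concern holds as a matter of estimand and possible bias. The cohort is selected on the primary outcome after exposure, and nothing shown for sub-study 2 corrects this. Whatever the effect pattern, the HR applies only from day 14 among those still in hospital, and early discharges do not count. Bias relative to all admissions depends on the pattern: essentially none under exactly proportional hazards without unmeasured heterogeneity, attenuation under a uniform 30% shortening, loss or reversal if benefit is concentrated in short stays, and slight strengthening if only long stays shorten. The documents do not show which pattern applies, so neither direction nor size can be stated as fact. The loss of events matters because the article itself warns that the dataset may be underpowered.

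**What to change.** Run the primary length-of-stay analysis on all psychiatric admissions that meet the other criteria, whatever their duration, and report the 14-day cohort as a sensitivity analysis. Change both the sentence under Inclusion and exclusion criteria and the Population row of Table 1.

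If the 14-day minimum is kept for length of stay, state the estimand as time to discharge among those still in hospital at day 14, report the number excluded in each group, and limit the conclusion to that. If it is kept for HoNOS change, state that this analysis too is conditional on a stay of at least 14 days, since it carries the same selection.

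The cost is small. All psychiatric inpatient spells are already to be extracted in order to classify C(E)TRs as community or inpatient. The downside is that brief crisis admissions enter the primary cohort; the 14-day sensitivity analysis shows their influence.

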### Identifying cases and controls

Using the review of clinical records of eligible patients previously described, we will measure whether each patient had a community C(E)TR within 6 months prior to their psychiatric hospital admission. We will form two groups: those who had a pre-admission community C(E)TR, and those who did not.

### Statistical analysis

#### Baseline descriptives

We will report the socio-demographic variables shown in online supplemental table 1, at admission (index date) and compare variables between those who had a pre-admission community C(E)TR and those who did not. As described in sub-study 1, frequencies and percentages will be obtained for categorical variables and mean (SD) or median (IQR) for continuous and count variables, according to their distributions. Data will also be presented separately for (1) People with intellectual disability and/or autism and (2) Autistic people without intellectual disability. Demographic and clinical characteristics will be compared using standard statistical comparisons for categorical (χ^2^) and continuous variables (t-test or Kruskal-Wallis).

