### Study eligibility criteria

Individuals of any age with a diagnosis of intellectual disability (ICD-10 code F7x) or autism (ICD-10 code F84) will be identified using diagnostic information entered into structured fields or in the free text record using the NLP diagnosis application. Participants must have a recorded diagnosis of intellectual disability and/or autism. Eligible participants must have received an episode of care from a community mental health service provided by SLaM for at least one continuous year between 1 January 2015 and 31 December 2023 to ensure that sufficient data are held in the record. All eligible episodes of care will be included, including those individuals with more than one period of community care of at least 1 year during this timeframe.

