### Matching a control group

We will match between one and five controls, who will not have a community C(E)TR, per patient who has a C(E)TR. Eligibility will be a diagnosis of intellectual disability or autism and having received a continuous period of community care within SLaM services for at least a year between 1 January 2015 and 31 December 2023. Matching will be based on age (±3 years), sex (male/female) and diagnosis (intellectual disability with/without autism, or autism without intellectual disability). Controls should be under an active episode of community care and not be an inpatient on the index date of their matched case. They must also have been under SLaM services for a similar total duration of their matched case (±2 years). Matching with replacement will be applied to ensure every case has an appropriate match according to these criteria. A pseudo-index date for each control will be assigned and will be the same as the index date of their matched case.

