### Statistical analysis

#### Descriptive statistics

We will report baseline socio-demographic variables for the C(E)TR and control groups (online supplemental table 1). Frequencies and percentages will be reported for categorical variables and mean (with SD) or median (with IQR) for continuous and count variables, depending on their distributions. We will describe these data separately for two diagnostic categories: (1) People with intellectual disability with/without autism and (2) Autistic people without an intellectual disability. We will compare the C(E)TR to the control group on these baseline socio-demographic characteristics using standard statistical comparisons for categorical (χ^2^) and continuous variables (t-test or Kruskal-Wallis). Descriptives of clinical variables and statistical comparisons between the C(E)TR and control groups will be provided separately for the 6 months before the index date and the 6 months after the index date. These descriptives will not lead to a causal interpretation of the effect of C(E)TRs.

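### In sub-study 2's stratified baseline descriptives, the first diagnostic stratum is the whole cohort, so the two strata overlap and none describes people with intellectual disability

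*Protocol article*

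**What the plan says.** Entry to the study is by diagnosis. Study eligibility criteria states: "Participants must have a recorded diagnosis of intellectual disability and/or autism". Table 1 gives the same condition for both sub-studies: "recorded diagnosis of intellectual disability (ICD-10 code F7x), autism (ICD-10 code F84) or both". Sub-study 2 adds a psychiatric admission of at least 14 days.

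The Baseline descriptives section of sub-study 2 first promises socio-demographic variables at admission, compared between people who did and did not have a pre-admission community C(E)TR. It then adds a breakdown by diagnosis: "Data will also be presented separately for (1) People with intellectual disability and/or autism and (2) Autistic people without intellectual disability".

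Elsewhere the article divides the population differently:

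- Descriptive statistics, sub-study 1: "1) People with intellectual disability with/without autism and (2) Autistic people without an intellectual disability".
- Matching a control group: "diagnosis (intellectual disability with/without autism, or autism without intellectual disability".
- Stage 1, propensity scores: the same two-level diagnosis variable as in the matching.
- Time-to-event analysis, sub-study 2: "relevant diagnosis at admission (intellectual disability with/without autism, or autism alone".

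**The concern.** A breakdown presented separately for two groups should place each patient in one group. Here the first group is described with the phrase that defines the whole study population. An analyst who follows the sentence literally would produce an overall table under a stratum label, plus a table for autistic people without intellectual disability. No table would describe people with intellectual disability.

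Comparing demographic and clinical profiles before admission is the first aim listed for sub-study 2, and the comparison of baseline demographics is a secondary outcome in Table 1. This sentence is also the only place where sub-study 2 specifies results by diagnosis. The replication site is to run both sub-studies and its data cannot be pooled with the main site's, so the same wording would be applied a second time.

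**Working it through.** The article states no figure that could be reproduced here. The check is one of set membership.

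**Step 1: the possible patients.** Under the eligibility criteria there are three diagnosis cells: A, intellectual disability only; B, intellectual disability and autism; C, autism only. The sub-study 2 cohort is A + B + C.

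**Step 2: assign each cell under each wording.**

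| Cell | Sub-study 2 descriptives, as written | Sub-study 1 descriptives, matching, propensity model, Cox covariate |
|---|---|---|
| A | stratum 1 | stratum 1 |
| B | stratum 1 | stratum 1 |
| C | strata 1 and 2 | stratum 2 |

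As written, stratum 1 = {A, B, C}, stratum 2 = {C}, and their overlap is {C}. Neither equals {A, B}. Under the wording used elsewhere, stratum 1 = {A, B} and stratum 2 = {C}, which are disjoint and cover the cohort.

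**Step 3: size of the overlap.** Let a be the share of the cohort in cell C. The two strata together hold 100% + a of the cohort, and a fraction a of stratum 1 is autism-only patients. The article does not give a. For assumed values of 20%, 40% and 60%, the strata sum to 120%, 140% and 160%.

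**Step 4: what could be recovered for {A, B}.** Let n be a stratum size, x a count, m a mean and s an SD, with subscripts 1 and 2 for the strata as written.

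- Size and counts: n₁ − n₂ and x₁ − x₂, hence percentages.
- Mean: (n₁m₁ − n₂m₂) / (n₁ − n₂).
- SD: the sum of squares in each stratum is (n − 1)s² + nm². Subtracting one from the other gives the sum of squares for {A, B}, and so its SD.
- Median and IQR: the quantiles of {A, B} are not determined by those of {A, B, C} and {C}, so they cannot be recovered.

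The last item matters because the section plans medians with IQRs for continuous and count variables where the distribution calls for them.

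**Step 5: which other analyses use the faulty grouping.** None does. The Cox model has its own, correctly defined diagnosis covariate. The HoNOS regression adjusts for baseline HoNOS, age, sex and ethnicity, with no diagnosis term. The pre-admission clinical and service use section names no diagnostic strata. Sub-study 1 is untouched.

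**The case against.** The strongest reply is that this is a slip of wording and not a choice of analysis. Presenting data separately makes sense only for disjoint groups. The sentence before refers back to sub-study 1, although that reference governs the summary statistics and not the strata. The Cox model in the same sub-study needs the exclusive two-level variable, so the analyst must build it in any case. All of this is fair, and it makes a drafting slip the likely explanation. It does not remove the contradiction: the sentence is a stated rule for a table, and nothing elsewhere in the article corrects it.

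It might also be said that a total plus a subgroup was intended. The total is already covered by the opening sentence of the section, and the addition of a separate presentation points to a split.

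Three stronger readings are tempting, and the article does not support them:

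- **That sub-study 2 yields no intellectual-disability result at all.** Only the stratified baseline descriptives are affected, and counts, percentages, means and SDs could be recovered by subtraction.
- **That a difference between diagnostic groups would be diluted.** A stratum 1 that includes cell C would indeed differ less from stratum 2. But the planned comparison is between people with and without a pre-admission community C(E)TR. No test or estimate of one diagnostic group against the other is planned, so no planned estimate is biased.
- **That the descriptives conflict with the Cox model in a way that harms the length-of-stay result.** A baseline summary is not set against a regression covariate in any planned analysis, and the covariate itself is defined correctly.

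**Conclusion.** The point holds in a limited form. As written, the first stratum in sub-study 2's baseline descriptives is the entire eligible cohort and contains the whole of the second. No separate intellectual-disability stratum is presented, and stratum 1 is not like for like with stratum 1 of sub-study 1. Medians and IQRs for people with intellectual disability would be lost. The size of the overlap depends on the autism-only share, which is unknown.

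This is a minor correction to a descriptive table. The length-of-stay and HoNOS analyses are unaffected. The conclusion assumes only that the sentence is followed literally and that the eligibility criteria apply to everyone in the hospital cohort, as Table 1 says.

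**What to change.** In the Baseline descriptives section of sub-study 2, define stratum 1 as people with intellectual disability, with or without autism, and leave stratum 2 as it stands. The strata then become disjoint and cover the cohort. They also agree with the sub-study 1 descriptives, the matching, the propensity model and the Cox covariate. Use the corrected definition at the replication site as well.

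The cost is one line of text. No further data or analysis is needed, because the Cox model already requires the same grouping variable.
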